#### 8.3.5 ADVERSE EVENT REPORTING

Study staff are tasked with promptly documenting incidents (AE or SAE) in the appropriate study's form and in the SYHealth's Incident Report. This report should detail the incident without disclosing any Health

Insurance Portability and Accountability Act (HIPAA) identifiers of the study participants. It should also include the site staff's actions, outcomes, and follow-up plans. The PI or study manager must report any incidents or adverse events in this study to SYHealth's Risk Management and to the DSMC within 48 hours. All AEs including SAEs will be reviewed by the DSMC and reported to the UCSD Human Research Protections Program and the assigned Risk Manager at SYHealth within 7 days of the event occurring and summarized in the annual progress report. Immediate reporting is required for SAE, injuries, or incidents for which medical costs are incurred, or breaches of Personal Health Information (PHI) confidentiality.

Such adverse events include but are not limited to:

- Mandatory reporting case
- Need to break confidentiality to report criminal (e.g., child maltreatment) behavior of a provider, care coordinator, or family member
- Inadvertent harm related to participation in the study
- Loss of data related to the trial for any reason.

---

### 8.3.6 SERIOUS ADVERSE EVENT REPORTING

Study staff will use the same protocol listed in 8.3.5 also SOP Adverse Events and Unanticipated Problems.

In the event of an emergency, the study team's immediate priority is to ensure that the participant received urgent medical care at the site or the nearest medical facility. Emergency contact information is available in clinics. In any crisis, staff should promptly contact the study coordinator or manager. They will decide whether to involve on-site medical staff of call 9-1-1. Immediate action is prioritized for participant safety before their departure from the premises. All emergencies, regardless of severity, must be reported to the SYHealth Risk management department, to the DSMC, UCSD-Institutional Review Board (IRB) and documented in CRF.

If a participant shows signs of a mental health emergency such as suicidal ideation, homicidal tendencies, or intoxication, study staff are trained to exercise judgment and sensitivity in these situations, consulting clinical decision-makers is necessary. Each SYHealth enrollment site has trained personnel to handle physical and medical emergencies. Emergency contact information is readily available in clinics. In any crisis, staff should promptly contact the study coordinator, manager or on-site medical provider. Immediate action is prioritized for participant safety before their departure from the premises. All emergencies, regardless of severity, must be reported to the SYHealth Risk management department to the DSMC and to the UCSD IRB. Documentation of the incident must be available in the participant's CRF.

---

### 8.3.7 REPORTING EVENTS TO PARTICIPANTS

**Not applicable**

---

### 8.3.8 EVENTS OF SPECIAL INTEREST

**Not applicable**

---

### 8.3.9 REPORTING OF PREGNANCY

**Not applicable**

## 8.4 UNANTICIPATED PROBLEMS

*Leave blank. Text should be included under the relevant subheadings below.*

### 8.4.1 DEFINITION OF UNANTICIPATED PROBLEMS (UP)

Study staff will use the same protocol listed in 8.3.5 also SOP Adverse Events and Unanticipated Problems.

The Office for Human Research Protections (OHRP) considers unanticipated problems involving risks to participants or others to include, in general, any incident, experience, or outcome that meets all of the following criteria:

- Unexpected in terms of nature, severity, or frequency given (a) the research procedures that are described in the protocol-related documents, such as the IRB-approved research protocol and informed consent document; and (b) the characteristics of the participant population being studied,
- Related or possibly related to participation in the research (“possibly related” means there is a reasonable possibility that the incident, experience, or outcome may have been caused by the procedures involved in the research), and
- Suggests that the research places participants or others at a greater risk of harm (including physical, psychological, economic, or social harm) than was previously known or recognized.

An UP is an adverse event unexpected in the research context, possible related to participation, and indicating higher risks than previously known.

### 8.4.2 UNANTICIPATED PROBLEM REPORTING

The investigator will report UPs to the reviewing IRB. The UP report will include the following information:

- Protocol identifying information: protocol title and number, PI’s name, and the IRB project number
- A detailed description of the event, incident, experience, or outcome
- An explanation of the basis for determining that the event, incident, experience, or outcome represents an UP
- A description of any changes to the protocol or other corrective actions that have been taken or are proposed in response to the UP.

To satisfy the requirement for prompt reporting, UPs will be reported using the following timeline:

- UPs that are SAEs will be reported to the IRB and to the DSMC within 7 days of the investigator becoming aware of the event.
- Any other UP will be reported to the IRB and to the DSMC within 7 days of the investigator becoming aware of the problem.
- All UPs should be reported to appropriate institutional officials (as required by an institution’s written reporting procedures), the supporting agency head (or designee), and the Office for Human Research Protections (OHRP) within 7 days of the IRB’s receipt of the report of the problem from the investigator.

### 8.4.3 REPORTING UNANTICIPATED PROBLEMS TO PARTICIPANTS

Not applicable

## 9 STATISTICAL CONSIDERATIONS

### 9.1 STATISTICAL HYPOTHESES

To evaluate the implementation and effectiveness of the multicomponent AI clinical intervention DRES-POCAI and its hypothesis all analyses will be performed at a patient level. Initially SYH will compare the intervention and control groups to determine if there was a significant (H2.1) increase in retinal screening uptake in the intervention group (primary outcome) and a corresponding (H2.2) increased diagnosis of DR (secondary outcome). The survey exploratory analyses will be performed to assess relationships between each item in the (H2.3) education questionnaire and the screening behavior (i.e., the proportion of patients with completed DR screen). These analyses will be used to identify items most strongly related to barriers and/or compliance, and thus, help refine the tool and guide future implementation strategies.

- **Primary Efficacy Endpoint(s):**

Primary **effectiveness** outcome — **DR screening completion**

Null hypothesis:  $H_0$ : There will be no difference in diabetic retinopathy screening rates between the intervention and standard of care study groups.

Alternative hypothesis:  $H_a$ : More participants in the intervention group will complete diabetic retinopathy screening compared to participants in the standard of care group.

- **Secondary Efficacy Endpoint(s):**

Secondary **effectiveness** outcome — **DR diagnosis**

Null hypothesis:  $H_0$ : There will be no difference in diabetic retinopathy diagnosis between the intervention and standard of care study groups. Alternative hypothesis:  $H_a$ : More participants in the intervention group will be diagnosed with diabetic retinopathy compared to participants in the standard of care group.

- **Exploratory analysis — identify knowledge, attitudes, and self-efficacy** factors associated with DR screening uptake. Analyses will be used to identify items most strongly related to barriers and/or compliance and guide future implementation strategies.

### 9.2 SAMPLE SIZE DETERMINATION

Sample size determination based on the primary outcome: Based on the hypothesis that SYHealth will see a minimum absolute screening increase of 10%, from 59% in the standard of care group to 69% in the intervention group of retinal screening uptake, and assuming an  $\alpha$  of 0.05 (significance), a  $\beta$  of 0.8 (power), the target enrollment for analysis is 772 participants (361 per arm). However, if after the initial refinement phase of the project it is determined that either a smaller or larger percent of the target population is currently completing DR screening we will adjust the study enrollment accordingly, to ensure we will have sufficient statistical power to evaluate the anticipated 10% increase in screening uptake. Assuming the screening rate of the target population will range from 45% to 65% (current estimate at 59%) the number of participants needed would range from 658 to 784 (current estimate 722). Anticipating up to a 10% attrition rate from consent to study intervention (participants who agree to participate and consent via phone, and either do not keep their appointment or who at the clinic appointment decide to withdraw from the study), we estimate the target enrollment will range from 732 to 872 (current estimate is 848 patients, 424 per arm) to ensure an analysis size of 722 participants (361 per arm) for a two independent sample Pearson chi2 test. Additionally, among the 2,514 patients who underwent retinal screening within the previous 12 months at the participating SYHealth clinics, 11% were diagnosed with DR; therefore, based on a screening uptake increase of 10%, a corresponding 16% increase in DR diagnosis (secondary outcome, H2.2) is anticipated in the intervention arm.

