## STATISTICAL METHODS

**Sample Size and Power Calculations:** Based on historical data from participating SYH clinics, we determined that approximately 59% of patients completed diabetic retinopathy screening, we powered our study to detect an increase of at least 10% in retinopathy screening completion (59% in the standard of care group to 69% in the intervention group), and assuming an  $\alpha$  of 0.05 (significance) and a  $\beta$  of 0.8 (power), we estimated that the target enrollment to detect this difference is 722 participants (361 per arm) using a two independent sample Pearson  $\chi^2$  test. Accounting for up to 15% attrition from consent to study intervention (participants who agree to participate and consent via phone, and either do not keep their appointment or who at the clinic appointment decide to withdraw from the study), we estimated as many as 848 patients (424 per arm) would need to be enrolled to ensure adequate sample size. To assess secondary outcomes, we determined that among the patients who underwent retinal screening within the previous 12 months at the participating SYH clinics, 11% were diagnosed with diabetic retinopathy; therefore, based on a screening uptake increase of 10%, a corresponding 16% increase in diabetic retinopathy diagnosis is anticipated in the intervention arm. However, if after the initial refinement

phase of the project, it is determined that either a smaller or larger percent of the target population is currently completing DR screening, we will adjust the study enrollment accordingly, to ensure we will have sufficient statistical power to evaluate the anticipated 10% increase in screening uptake.

**Statistical significance and transformation of variables:** All statistical tests will be two-sided unless defined otherwise. Statistical significance will be set at  $p$ -value  $<0.05$ . Where distributional assumptions are necessary for the correct evaluation of statistical results, appropriate description, diagnostic evaluation, and (if required) transformation of variables will be carried out. In the event the parametric tests indicated are unable to be used, non-parametric versions will be used.

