| Description of Sites/Facilities Enrolling Participants: | Enrollment sites for the study will include two primary care clinics within SYHealth's service network, SYH-CV and SYH-KC. The two selected clinics are in the South and Central regions respectively. These sites serve two of SYHealth's primary service areas with the highest prevalence of DM. SYH-CV is the medical home to more than 24,000 patients (~13% with a diagnosis of DM). The clinic is in the second largest city in San Diego County, with approximately 75% of its residents identifying as Hispanic/Latino, and 13% of the population living below 100% of the federal poverty level (FPL). SYH-KC serves as a medical home for more than 9,000 patients (~14% with a diagnosis of DM). The clinic is situated in a community with primarily racial and ethnic minority residents of color (SYHealth population ~60% Hispanic/Latino and 16% Black), with 14% of the residents in this community living below the 100% FPL and disproportionately impacted by social determinants of health (SDoH). SYHealth's quality metrics of these two clinics reflect high prevalence of DM, and conversely, poor disease management. For example, DR screening (46%) is significantly low and demonstrates a need for further improvement of clinical practices/workflows.                                                                                                                                                                                                                                                                                                                                                                                                                                                                                                                                                                                                                    |

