### 5.1 INCLUSION CRITERIA

This study targets active SYHealth patients with diabetes mellitus (DM) who have not had a retinal exam in the last 11 months. The study will recruit and randomize a cohort of 848 adults (424 per arm) from SYHealth-Chula Vista and SYHealth-King-Chavez clinic sites. In order to be eligible to participate in this study, an individual must meet all of the following criteria:

1. Provision of signed and dated informed consent form.
2. Stated willingness to comply with all study procedures and availability for the duration of the study.
3. Established and active patient of SYHealth-CV and KC (having a medical appointment in the last 18 months).
4. Person aged 22 and older.
5. Established diagnosis of DM.
6. Medical appointment(s) (in-person or telehealth) scheduled during the intervention period.
7. Has not completed a dilated eye exam or retinal exam in the last 11 months.
8. Be able to read, understand, and speak English or Spanish at a level sufficient to consent to participation, comprehend educational materials and sessions, and complete surveys.

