#### 9.4.2 ANALYSIS OF THE PRIMARY EFFICACY ENDPOINT(S)

**Primary Endpoint: Increase in Retinal screening completion (H2.1)**

**Measurement:** Boolean variable (Yes/No) indicating completion of retinal screen within the defined study period (60 days from randomization).

**Scale:** Binary

**Analysis:** Chi-squared test or logistic regression will be used to compare screening completion rates between intervention and usual care groups. Regression covariates may include demographics and baseline clinical factors. Covariate selection will aim for a parsimonious model to achieve clarity and avoid overfitting. We will evaluate the intervention effectiveness across subgroups/categories by including a risk group classification variable in our models (to determine if there are differences in outcomes by group). If these risk groups are determined to confound the relationship between intervention and outcome, we will then stratify our analysis.

**Results Presentation:** Adjusted odds ratios with 95% confidence intervals will be reported.

**Assumption Checks:** When logistic regression is used, the data will be assessed for linearity, absence of multicollinearity, and influential outliers.

**Populations:** All enrolled participants will be included in the analysis.

**Missing Data:** Multiple deletion or imputation methods will be used to handle missing data depending on the pattern of missingness, e.g. if entire surveys are missing if missingness is driven by specific items or response groups in the survey, and/or if the data is missing completely at random. We have allowed for a 10% dropout/withdrawal rate between enrollment and intervention, and thus can use pairwise or listwise deletion of up to 10% of participants and still maintain adequate power for analysis.

**Outliers/Non-adherence:** Data outliers will be assessed to ensure they are not the result of data entry or measurement error. True data outliers will be handled either by trimming, adjusting the weight of the outliers, or by using robust regression techniques. Non-adherence will be addressed by analyzing data per-protocol in addition to intent to treat.

---

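### Protocol 9.2 prints 772 where 722 is meant, and its target of 848 follows from the SAP's 15% attrition, not from its own 10%; the 80% power stands

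*Combined protocol and SAP*

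**What the plan says.** **Analysis size.** Protocol 9.2 plans for a rise "from 59% in the standard of care group to 69% in the intervention group of retinal screening uptake", at a 0.05 significance level and 80% power, and says "the target enrollment for analysis is 772 participants (361 per arm". Later in the same paragraph the analysis size is given twice as 722, once with 361 per arm. The SAP (Sample Size and Power Calculations) also has 722, 361 per arm.

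**Attrition and enrolment.** Protocol 9.2: "Anticipating up to a 10% attrition rate from consent to study intervention". It gives an enrolment range of 732 to 872 with a current estimate of 848. The SAP: "Accounting for up to 15% attrition from consent to study intervention", again leading to 848. The protocol's missing-data text in 9.4.2 says "We have allowed for a 10% dropout/withdrawal rate between enrollment and intervention", and 9.4.3 and 9.4.9 repeat it. The SAP's missing-data paragraph has 15%.

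**What 848 counts.** Protocol 5.1: "The study will recruit and randomize a cohort of 848 adults (424 per arm". The SAP and protocol 9.2 speak of 848 enrolled, before a loss that they define as people who consent by phone and then miss the appointment or withdraw at it.

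**Baseline rate.** The SAP reports from the clinics' historical data that "approximately 59% of patients completed diabetic retinopathy screening". The synopsis says of the same two clinics that "DR screening (46%) is significantly low". Protocol 9.2 considers baseline rates from 45% to 65% and undertakes to adjust enrolment if the rate proves different.

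**The concern.** The sentence that defines the analysis size contradicts its own per-arm figure. The next step, from analysis size to enrolment, cannot be reproduced from the attrition rate stated beside it. This is easy to miss because 848 lies inside the printed range of 732 to 872, although range and central value rest on different rates.

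Three working decisions depend on these figures: when recruitment stops, how much listwise deletion the plan treats as harmless (10% in the protocol, 15% in the SAP), and how far enrolment moves if the 9.2 adjustment rule is used. That rule also needs to know which baseline rate governs, and the documents print 59% and 46% for the same clinics without giving a definition, period or denominator for either.

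**Working it through.** **Inputs.** Control 59% and intervention 69% (SAP; protocol 9.2); two-sided 0.05 (SAP); power 0.80; 1:1 allocation; Pearson chi-squared test (both documents); attrition 10% (protocol) or 15% (SAP).

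**1. The plan's own analysis size.** Using the pooled-variance formula without continuity correction,

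n per arm = [1.960·√(2·p̄·(1−p̄)) + 0.842·√(p₁(1−p₁) + p₂(1−p₂))]² / (p₂−p₁)²

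With p₁ = 0.59, p₂ = 0.69 and p̄ = 0.64: [1.960·√0.4608 + 0.842·√0.4558]² / 0.01 = 360.5, so 361 per arm and 2 × 361 = 722. Power at 361 per arm is 80.1%. The plan's figure is reproduced exactly. A continuity correction gives 381 per arm (762) and a one-sided test 284 (568), so neither explains 772.

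**2. The planned range of analysis sizes.** 65% against 75% gives 658 and 45% against 55% gives 784, both as printed in 9.2.

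**3. From analysis size to enrolment, N/(1 − attrition), rounded up.**

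| Analysed | at 10% | at 15% | printed in 9.2 |
|---|---|---|---|
| 658 | 732 | 775 | 732 |
| 722 | 803 | 850 | 848 |
| 784 | 872 | 923 | 872 |

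Both ends of the printed range come from the 10% column and the central value from the 15% column. Per arm, 361/0.85 = 424.7, which rounded down is 424, or 848 in total.

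**4. Power under each reading of 848, at 59% against 69%.**

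- 848 enrolled, 15% lost: 848 × 0.85 = 721 remain, power about 80%.
- 848 enrolled, 10% lost: 848 × 0.90 = 763, about 382 per arm, power about 82%.
- 848 randomised and all analysed: 424 per arm, power about 86%.

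**5. If 46% were the control rate.** 46% against 56% needs 392 per arm, 784 in total (enrolment 872 at 10% attrition, 923 at 15%). Power is about 77% at 361 per arm, 79% at 382 and 83% at 424.

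**The case against.** The strongest reply is that these are slips of text with no consequence. Nothing is computed from 772. The target of 848 is the same in the SAP, the synopsis and protocol 5.1 and 9.2, and it follows from the SAP's 15%. If true attrition is 10%, the mismatch enrols more people than needed, not fewer. The synopsis offers 46% as an example from quality metrics and never calls it a control rate; it lies inside the 45% to 65% range that 9.2 already plans for. All of this stands, and it limits the point to consistency.

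Three stronger readings are tempting, and the documents do not support them.

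- *That neither 80% power nor 848 has a basis.* The power is exact for the stated inputs, and 848 follows from the SAP. Only the protocol's own step from 10% to 848 fails.
- *That the trial has 77% power.* This needs both 46% as the true control rate and only 361 per arm analysed. If the 848 that 5.1 says are randomised are all analysed, power is 83% at that rate.
- *That 59% is a 12-month rate in all diabetic patients, so power collapses over the shorter endpoint window.* The clinic sizes give about 24,000 × 13% + 9,000 × 14% = 4,380 patients with diabetes, and 2,514 screened in 12 months would be 57%. These counts are approximate, and they sit closer to 59% than to 46%. A much lower base rate would also raise power for a 10-point difference: as an illustration, 20% against 30% gives 87.5% at 361 per arm.

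It can also be said that attrition is not purely a loss before randomisation. Protocol 4.2 and 8.1 place randomisation after on-site consent and surveys, so missed appointments fall before it. Withdrawal at the visit could fall on either side, and protocol 7.2 foresees people who are randomised but do not receive the intervention. That is a reason to ask what 848 counts, not to assert that only 722 need be randomised.

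**Conclusion.** The point holds as a correction of figures in protocol 9.2. The 772 is wrong by 50. The enrolment target exceeds what the stated 10% attrition implies by 45 (848 against 803), and it is paired with a range built on the other rate. The SAP and protocol disagree on attrition and so on the deletion allowance.

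Power for the planned comparison is as claimed, and the mismatch does not underpower the trial. Depending on whether 848 counts consented or randomised participants, and on the loss, power at 59% against 69% lies between about 80% and 86%.

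The 46% and 59% remain unreconciled. This matters only if 46% describes the trial's control arm, which the documents do not say.

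All power figures assume the pooled chi-squared calculation, equal arms and a 10-point absolute difference.

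**What to change.** 1. In protocol 9.2, print 722 in place of 772.
2. State one attrition rate in the SAP and in protocol 9.2, 9.4.2, 9.4.3 and 9.4.9, and make target and range match it: at 15%, about 850 with a range of about 775 to 923; at 10%, about 803 with a range of 732 to 872. The documents give no reason to prefer one rate beyond the fact that 848 matches 15%.
3. Say whether 848 counts consented or randomised participants, bring 5.1, 9.2 and the SAP into line, and state the matching power at 59% against 69%: about 80% if 722 are analysed, about 86% if all 848 are.
4. Give the definition, time window and denominator of the 46% and of the 59%, and say which one the adjustment rule in 9.2 uses. If 46% applies to the control arm, report the power in step 5 of the working.

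Items 1 to 3 are text edits. Item 4 means tracing two figures to their source in the clinics' data; the documents do not show how much work that is. Keeping 848 needs no additional participants. Moving to a consistent 15% changes the central target by two.
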